#### Exclusion criteria

Physiotherapists should exclude patients with “red flags”: symptoms that suggest a serious illness or spinal abnormality, including serious trauma to the neck and no X-ray, preceding neck surgery, osteoporosis, myelopathy, history of cancer, unexplained weight loss, current fever, history of infections, constant and progressive non-mechanical pain, insidious progression of pain, signs of spinal cord compression (neurological examination to exclude spinal cord or cervical myelopathy such as clumsy hands, altered gait, or disturbances in sexual, bladder, or sphincter function).

#### Development of the implementation strategy based on expected barriers

Barriers to implement evidence-based interventions in physiotherapy have been identified and are, for example, lack of time, lack of high-quality research, confusion, and misperceptions of the new method [19]. Identified facilitating factors are, for example, approval by management [34], outreach visits [29], and fast support and training for the users if new technology will be introduced [35]. These barriers and facilitators [19, 20, 35] have been considered in the development of the implementation activities for successful uptake of the NSEIT and NSE among physiotherapists. The barriers expected and the planned activities to overcome these are described in Table 1.

**Table 1 Tab1:** Barriers and activities to minimize the barriers impact in the implementation of NSEIT

Barriers	To overcome barriers	Benefits
Physiotherapists in primary care have limited time for education and learning new methods	Before implementation starts, inform manager and acquire permission to implement NSEIT	Fewer individual visits to physiotherapists will save time
Physiotherapists need time to practice the new exercises and to master NSEIT	Inform physiotherapists and manager that some extra time is needed at the beginning	Will save time due to fewer individual visits
Patients or physiotherapists have problems with the Internet-based program (NSEIT)	The web-based platform INERA is supported by the Regions in Sweden. The physiotherapist can call for support	Fast support will facilitate the use of NSEIT
Physiotherapists forget to use NSEIT if there are long intervals between patients	Repetition of the neck-specific program after one and 3 months in group A (experimental group).	Will remind the physiotherapist to use NSEIT
Physiotherapists forget how to use neck exercises and/or NSEIT	Repetition of the neck-specific program after one and 3 months in group A (experimental group).	Repetition of instruction on how the exercise will be performed.
Physiotherapists have questions about the exercises and/or NSEIT	Support from the facilitators by chat and on-line meetings in group A (experimental group).	Enhanced confidence in using the method

### Procedure

The 20 physiotherapy clinics will be randomized to 2 groups, stratified for the number of physiotherapists working at the clinic (≥4 physiotherapists or 3 physiotherapist). A computerized block randomization list, conducted by a statistician and allocated by a project team member, will be used. The randomization will be performed by an independent researcher. The researcher sends an e-mail to all physiotherapists at the clinic, containing information about the randomization group. Due to the nature of the study can the physiotherapist not be blinded. Any change in the protocol will be communicated with the ethics committee and if approved appropriate changes will be made in the ClinicalTrial.gov Registry.

### Recruitment of physiotherapy clinics and patients

In the first step, physiotherapy clinics will be recruited through contact with health care providers and research coordinators in county councils in Sweden. In the second step, an oral on-line presentation describing the study will be given to those health care providers that express interest in the study. If the eligible physiotherapy clinic confirms participation via e-mail after the presentation, physiotherapists will be included after written informed consent. Registered physiotherapists working at the included physiotherapy clinics will screen patients for eligibility by taking a detailed medical history and careful clinical examination, following the regulations for registered physiotherapists in Sweden (Health and Medical Services Act 2017:30 [36] and the patient security law (SFS 2010: 659. Patientsäkerhetslag. Stockholm: Socialdepartementet) [37]. Patients with neck pain deemed to benefit from the NSE or the NSEIT and who are willing to participate in the study will be included. If the eligible patient confirms participation, written and informed consent will be completed through Health Care Guide 1177 (a national hub for health care information and services in Sweden) and patients logging in using BankID. Before completing the consent form, potential participants (physiotherapists and patients) will read the information, describing the purpose of the study, data collection process, duration of commitment, intervention, and benefits and harms of the treatment. The information also explains that participants can withdraw from participation at any time of the study. Patients are insured by the County Council Mutual Insurance Company, a mutual insurance company that covers patient injury (compensation to those who suffer harm) for all public health care providers and private providers contracting with the Swedish government.

#### Implementation study – education and practical training of physiotherapists

Physiotherapists in both group A (the experimental group) and group B (the control group) will receive on-line theoretical education including 3 hours of practical training by the project leaders. The standardized theoretical instruction includes three 45-minute on-line lectures (Table 2). It will be followed by 3 hours of practical training, including clinical examination in patients with neck disability and instructions on how to perform the neck-specific exercises. The project leaders developed the education program, based on the education used in our earlier studies [11, 12, 23, 38], and the physiotherapists will receive practical training from physiotherapists well used to the exercise intervention and internet-based program. The physiotherapists will be informed that NSEIT was non-inferior to NSE in the RCT and that the research findings targeted WAD grades II and III. The physiotherapist will not be prohibited from using NSEIT for other patients with neck pain. To facilitate the implementation process, group A will receive additional support: the physiotherapists will be able to contact the project leader via chat. The physiotherapists in group A will also have two on-line workshops after one and 3 months (2 × 45 minutes); see Table 2. Physiotherapists in group B will not receive additional support or education after the first three theoretical on-line lectures and the 3 hours’ practical education.

**Table 2 Tab2:** Implementation component

Implementation education	Content
Lecture 1	• Introduction to the neuromuscular function of the neck
	• Current evidence for exercise in neck pain and WAD
	• Results of the previous two RCTs regarding NSEIT and NSE
	• Information about the progression of the exercise program
Lecture 2	• The whiplash injury mechanism and causes of general neck pain
	• Relevant musculoskeletal anatomy and function
	• Biopsychosocial factors in persisting pain
	• Neurophysiological and neurobiological processes underlying chronic pain
	• Strategies for dealing with neck pain relapse
	• Theoretical base for the medical history and clinical examination
	• How to measure neck muscle endurance and clinical signs of neuromuscular neck dysfunction.
Lecture 3	• Information on how to use the internet-based program
	• Practical training in the use of NSEIT in the test version
Practical training	• Face-to-face meeting with physiotherapists at the clinic
	• Practical training in clinical examination of neuromuscular dysfunction and neck muscle endurance
	• Practical training in neck-specific exercise
Workshop 1	• Discussion regarding difficulties experienced in using NSEIT/NSE and to share information with other physiotherapists; for example, regarding the progression of the exercises and patients with sustained pain.
Workshop 2	• Discussion regarding difficulties experienced in using NSEIT/NSE and to share information with other physiotherapists; for example, regarding the progression of the exercises and patients with sustained pain.

### NSE and NSEIT - the implementation object

#### Neck-specific exercise with internet support

The internet-based exercise program, NSEIT, is available on-line by phone, tablet, or computer via the Swedish National Support and Treatment Services, INERA. Since 2016, all regions in Sweden have been connected to the Support and Treatment services, a web-based e-health solution to enhance digitalization in health care. The platform is accessed through Health Care Guide 1177 and patients logging in using BankID. The physiotherapists logging in to the Support and Treatment services will choose exercises and information from two different programs, WAD ExerciseIT (for patients with whiplash-associated disorders) and Neck ExerciseIT (for patients with non-specific neck pain). The two programs contain the same neck-specific exercises and the same information about persistent pain, the benefits of exercise directed to the deep neck muscles, strategies for dealing with neck pain relapse, ergonomic advice related to the neck, complementary exercises for shoulder muscles and the low back, and strategies for continuing exercise after the treatment period. WAD ExerciseIT contains information about whiplash injury and Neck ExerciseIT has information about non-specific neck pain and stretching exercises. The physiotherapists will choose and individually progressively assign the neck-specific exercises during the treatment period. In the RCT study, each patient had 4 meetings with the physiotherapist, at weeks 1, 2, 3, and 7, to ensure that the patient performed the exercises as intended [12]. At week 1, the first visit to the physiotherapist included an introduction to the exercise intervention chosen from a clear and written framework of exercises. The physiotherapist introduced exercises aimed to facilitate activation of the deep neck muscles and information about the importance of good body and neck posture to minimize postural strain. At week 2, they introduced isometric neck-specific exercises in supine position and continued them in sitting position. Weeks 3 to 12 involved continued training with gradual progression, using a rubber band in sitting position. The patient could also exercise at a gym, using a weighted pulley or guild board. The physiotherapists will be informed about the four meetings in the RCT study, but in this implementation study the physiotherapists will be free to book appointments with the patients.

#### Neck-specific exercises with regular visits to the physiotherapy clinic

Physiotherapists will also be able to use the NSE in their clinic for patients who need or would like supervised training; all the NSE exercises and information will be available on paper. The patients will receive the same information and exercise as in the NSEIT program, but it will be delivered by a physiotherapist. Patients will not be withdrawn if they receive any other physiotherapy treatment (for example acupuncture or manual treatment) in combination with the NSEIT/NSE.

### Measurements

Outcome measurements will be recorded at baseline and after 3 and 12 months. See Fig. 2 for the planned schedule of enrollment, interventions, and assessments, and Table 3 for the relationship between the RE-AIM framework and data collection. All questionnaires will be answered electronically through a website. Physiotherapists and patients will receive a disposable code e-mailed by a project team member to log in to the System Artrologik (Survey&Reports). Patients will answer the baseline and 3-month questionnaires through the Support and Treatment services and the 12-month questionnaire through the System Artrologik. The electronic questionnaire cannot be submitted if the core outcomes are not answered. If a participant does not answer the questionnaire after two reminders (1.5 weeks after it is due and after another 1.5 weeks), a project team member not involved in the randomization will contact the participants and remind them.

**Table 3 Tab3:** RE-AIM framework and data collection

Dimension	Research question	Data Collection
Reach	To what extent do patients with WAD receive NSEIT/NSE in primary care?	Primary outcome Data from the medical record from each included physiotherapy clinic and/or the web-based platform INERA
Effectiveness	Is the NSEIT/NSE program effective at decreasing disability and pain in patients with WAD or non-specific neck pain in primary care? Will the results be the same as in the RCTs at 3 and 12 months of follow-up?	Primary and secondary outcomes. Patient self-reported outcomes. The results will be compared with those of previous studies.
Adoption	To what extent do the physiotherapists apply the NSEIT/NSE to patients with WAD or non-specific neck pain?	Secondary outcomes Physiotherapist-reported outcomes. Qualitative methods
Implementation	To what extent is the intervention delivered according to the NSE protocol (fidelity)?	Qualitative methods
Maintenance	To what extent will physiotherapists be continuing to use NSEIT/NSE at the 12-month follow-up?	Secondary outcomes Physiotherapists reported outcomes Qualitative Methods

#### Implementation

Background data on each physiotherapist will be collected and include age, sex, years working as physiotherapist, and post-secondary education in physiotherapy.

#### Primary outcome

The primary outcome will be the proportion of patients with neck pain receiving neck-specific exercise during the intervention period. Data will be collected from each included physiotherapy clinic, based on each physiotherapist’s registered ICD-10 code (S134, S134A, S134B, S134C, T918, M501, M502, M503, M530, M531, M542) in the medical record.

#### Secondary outcome

The Evidence-Based Practice Attitude Scale (EBPAS) will be used to assess the physiotherapists’ attitudes to implementation of evidence-based practice [39] and will be collected only at baseline. The questionnaire includes 15 items, each answered on a 5-point scale from 0 (not at all) to 4 (agree completely). The total score ranges from 0 to 60, and higher scores indicate more favorable attitudes. The questionnaire can be divided into four different scales: scale 1 (requirements), scale 2 (appeal), scale 3 (openness), and scale 4 (divergence). Self-efficacy and confidence in diagnosing and treating patients with neck pain will be measured by use of the Practitioner Confidence Scale (PCS) [40]. The PCS will be collected before and directly after the theoretical and practical education, and at the 3- and 12-month follow-ups. A total of 4 items are reported by the practitioner and a total score is collected, where 4 represents greatest self-confidence and 20 represents lowest self-confidence.

The secondary outcome measures will also include questions about each physiotherapist’s experience of the neck-specific program: the number of times the physiotherapist had contact with the patient (visits, telephone, and/or chat) and information about additional or other exercises and/or treatment for neck pain will be collected via the medical record and/or the web-based support and treatment platform INERA, and/or through the Swedish Classification of Health Interventions [41].

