### Statistical analyses

All analyses will be conducted in collaboration with a statistician. Data will be analyzed according to intention to treat and supplemented with per protocol analysis. An analysis will be done of the missing data. Imputation methods may be used when deemed to have additional value. Subgroup analyses of age, gender, neck pain intensity, headache, and dizziness may possibly be performed.*Data regarding the implementation strategy* will be analyzed using a parametric t-test and a linear mixed model or repeated-measures ANOVA or the non-parametric Mann-Whitney U test and Kruskal-Wallis test, depending on the data. Analyses will evaluate differences between groups A and B and changes in variables over time.*Data regarding the effectiveness of NSEIT and NSE* will be analyzed with a linear mixed model or repeated-measures ANOVA or Kruskal-Wallis, depending on the data. NDI, pain intensity, headache, and dizziness will be evaluated as dependent variables with time as an independent fixed factor (baseline, 3 months, and 12 months after start of intervention). The results will be compared with the results from the RCT studies [8, 12].

The effect of neck-specific exercises in the present study for WAD grades II and III and for patients with other neck-pain disorders will also be evaluated and compared with the results in the RCT studies [8, 12].

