### Sample size

Sample size and power regarding group differences were calculated by a statistician. The aim of the study is to evaluate both implementation and effectiveness. The sample size calculation to evaluate implementation was based on the assumption that 15% more patients will receive neck-specific exercises in the intervention group (40% in the intervention group and 25% in the control group). The required sample size under individual randomization will be 150 patients in each arm. With 10 physiotherapy clinics (clusters) in each arm (a total of 20 clusters), intra-cluster correlation of 0.02 and a cluster size of 21 patients, a total of 420 patients will be recruited for 80% power and a significance level of 0.05. To ensure that enough people are in each group after dropouts, a total of 500 patients will be included, 25 patients from each cluster.

Sample size calculation to evaluate effectiveness was based on a clinically relevant improvement of 7% in the NDI, an effect size of 0.2 (Cohen’s f) or 0.4 (Cohen’s d), a correlation among repeated measures of 0.3, and the need for a total of 56 participants for 80% power and a significance level of 0.05. With an expected dropout rate of 20%, a total of 70 participating patients will be needed. The total number of patients may be more than 70 because patients will be recruited at each clinic.

Repeated-measure ANOVA or a linear mixed model will be used to examine changes in the patient-reported outcomes over time (i.e., at baseline and 3 and 12 months). The results will be compared with the results from the RCT studies [8, 12]. Patients who are included in both the intervention and control implementation groups and receive neck-specific exercises will be treated as one group in terms of the effect of the intervention. Analyses will be performed with parametric statistics if assumptions of normality are met, and otherwise with non-parametric statistics.

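### The confidence scale (PCS) is measured twice before the arms' support diverges, but the listed A-versus-B tests do not state that these scores serve as baseline; fixing the contrast would gain precision at almost no cost.

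*Protocol article*

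**What the plan says.** The Secondary outcome section (implementation) gives the PCS schedule: "The PCS will be collected before and directly after the theoretical and practical education, and at the 3- and 12-month follow-ups".

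The section on education and practical training shows where the arms part: "Physiotherapists in both group A (the experimental group) and group B (the control group) will receive on-line theoretical education including 3 hours of practical training". After that, group A can reach the project leader by chat and attends workshops at one and 3 months. For the control arm, "Physiotherapists in group B will not receive additional support or education after the first three theoretical on-line lectures" and the practical session.

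The Statistical analyses section covers all implementation data in one sentence. These data "will be analyzed using a parametric t-test and a linear mixed model or repeated-measures ANOVA or the non-parametric Mann-Whitney U test and Kruskal-Wallis test". Which of these applies is left to how the data turn out. The target follows: "Analyses will evaluate differences between groups A and B and changes in variables over time". No covariate is named, no PCS score is identified as the reference, and the model term that tests the added support is not stated.

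**The concern.** For the A-versus-B comparison, the PCS before training and the PCS directly after training are both pre-support values. They should predict later confidence and can remove between-person variation from the comparison. The listed analyses differ in what they do with them:

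- A t-test or Mann-Whitney test at a follow-up visit discards them.
- A repeated-measures model takes them in as outcomes. The result then depends on the term that is read. The group main effect averages in two occasions at which the support has not yet been given; the group-by-time term does not have this problem.
- The time effect pools the arms and includes the jump from training that both arms had. The Background cites a prior implementation study in which instruction alone was followed by sustained higher confidence, so some improvement over time is to be expected in both arms.

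At stake is the precision of the between-arm comparison on the one physiotherapist-rated scale scheduled after the arms diverge (the attitude scale is taken at baseline only), together with a clear separation of that comparison from the effect of the common training.

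**Working it through.** **The plan's own figures.** The article gives no power or sample size for the PCS. Its patient sample size reproduces. With unpooled variance, (1.960 + 0.842)² × (0.40 × 0.60 + 0.25 × 0.75) / 0.15² = 149.1, so 150 per arm. The design effect is 1 + 20 × 0.02 = 1.4, and 150 × 1.4 × 2 = 420. None of this concerns the PCS.

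**Inputs.**
- From the article: four PCS occasions, two of them before the support diverges; 10 clinics per arm; at least 3 physiotherapists per clinic, hence n = 30 per arm as a minimum if all take part.
- Assumed: effect d = 0.6 SD at both 3 and 12 months and zero before; SD 1; equal correlation ρ between occasions, 0.3 to 0.7; no clustering; two-sided 5% level.

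**Formulas.** Power ≈ Φ(effect / √(2v/n) − 1.96), where v is the variance of the quantity compared.

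| Analysis | Effect | v | v at ρ = 0.5 |
|---|---|---|---|
| t-test at 12 months | 0.6 | 1 | 1 |
| Group main effect, four occasions | (0 + 0 + 0.6 + 0.6)/4 = 0.3 | (1 + 3ρ)/4 | 0.625 |
| Unadjusted mean of 3 and 12 months | 0.6 | (1 + ρ)/2 | 0.75 |
| Group-by-time, mean late minus mean early | 0.6 | 1 − ρ | 0.5 |
| 12-month ANCOVA on both early scores | 0.6 | 1 − 2ρ²/(1 + ρ) | 0.667 |
| Mean of 3 and 12 months, adjusted for both early scores | 0.6 | (1 + ρ)/2 − 2ρ²/(1 + ρ) | 0.417 |

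Worked case, 12-month ANCOVA at ρ = 0.5: √(2 × 0.667/30) = 0.211; 0.6/0.211 = 2.85; Φ(2.85 − 1.96) = 81%. For the t-test: √(2/30) = 0.258; 0.6/0.258 = 2.32; Φ(0.36) = 64%.

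**Results, power in %.** Simulated values (20,000 runs), where available, are in brackets.

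| Analysis | ρ = 0.3 | ρ = 0.5 | ρ = 0.7 |
|---|---|---|---|
| t-test at 12 months | 64 (63) | 64 (63) | 64 (62) |
| Group main effect, four occasions | 39 (38) | 31 (31) | 26 (25) |
| Unadjusted mean of 3 and 12 months | 82 | 77 | 71 |
| Group-by-time, 1 df | 79 | 91 | 99 |
| Group-by-time F test, 3 df | (63) | (79) | (96) |
| 12-month ANCOVA | 71 (68) | 81 (79) | 95 (93) |
| Adjusted mean of 3 and 12 months | 90 (88) | 95 (94) | 99 (99) |

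From the unrounded simulated values, the 12-month ANCOVA gains 68.1 − 63.0 = 5.1 points over the t-test at ρ = 0.3 and 93.1 − 62.3 = 30.8 points at ρ = 0.7. Against the 3-df group-by-time test it gains 68.1 − 62.9 = 5.2 points, 79.1 − 78.9 = 0.2 points, and loses 95.5 − 93.1 = 2.4 points at ρ = 0.7. The adjusted mean gains about 11, 4 and under 1 points over the 1-df group-by-time contrast.

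**Bias.** A second simulation (1,500 runs, 40 per arm, true effect 0.50, ρ = 0.5) gave mean estimates of 0.494 for the unadjusted mean of both follow-ups, 0.501 adjusted, 0.504 for group-by-time and 0.242 for the four-occasion main effect. Only the last is diluted.

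**The case against.** A reader might infer that the planned analyses will dilute or miss a real effect of the extra support. The text does not support that. Halving occurs only if the four-occasion group main effect is taken as the A-versus-B test, and the Statistical analyses section does not say so. It names model families and two broad targets, and a group-by-time term is at least as natural a reading. A follow-up t-test is unbiased. It is also listed together with the mixed model or repeated-measures ANOVA, in a sentence that serves all implementation outcomes, so it need not be the PCS test. This stands, and it limits the point to precision and clarity.

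A reader might also infer that the article rejects adjustment. It is silent, and an analysis plan that is not shown may settle the covariates and the model term. This stands too, so the point is an improvement to the tests that are named and not a charge of omission.

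Nor does any passage say that pooled change over time will be credited to the extra support. The common training is itself listed as an implementation component in Table 2, and measuring confidence directly after it is intended. The request is only to keep the two results apart.

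Three further cautions apply. Physiotherapists are e-mailed their allocation, and its timing relative to the first two PCS scores is not given, so these scores precede the support but perhaps not knowledge of the arm. The second workshop falls at 3 months, so the 3-month effect may be smaller than the 12-month effect, and the gain from averaging the two visits may be overstated. Part of the distance from 63% to 94% at correlation 0.5 comes from averaging two visits rather than from adjustment: the unadjusted mean alone reaches about 77%.

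What remains is that the non-parametric route has neither an adjustment nor an interaction, that the t-test at follow-up has no adjustment, and that the listed targets do not name the contrast that this schedule makes possible.

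**Conclusion.** The point holds as a low-cost improvement on a secondary outcome, not as an error in the plan. Two of the four PCS scores precede the divergence in support, and the listed A-versus-B tests do not state that they are used as baseline. Follow-up-only tests lose precision without bias; a four-occasion main effect, if chosen, would halve the effect; a group-by-time contrast would not. The gain of the 12-month ANCOVA over the 12-month t-test is about 5 to 31 power points, and it is small or absent against a group-by-time test. These figures rest on assumed values for effect, correlation and number of physiotherapists, and ignore clustering. With 0.5 SD, 30 to 50 per arm and a clinic correlation of 0 to 0.05, the order of the main alternatives is the same: single-visit t-test 45 to 71%, four-occasion main effect 18 to 44%, group-by-time from 60% and adjusted mean from 73%, both up to more than 99%.

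**What to change.** For the PCS, state that the A-versus-B contrast is the group difference at 3 and 12 months in a linear mixed model with those two occasions as outcomes, adjusted for the PCS before training and directly after training, with clinic as a random effect because clinics are randomized. An explicit group-by-time contrast of late against early occasions, also with clinic as a random effect, would be an acceptable equivalent. Report the change from before to directly after training separately, as the effect of the training common to both arms.

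The cost is a change of wording. All four measurements are already scheduled. The model spends two degrees of freedom on the covariates, and physiotherapists with a missing early score need a simple stated rule, such as baseline imputation.
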